## 5.2 Inclusion Criteria

- Age > 18 years
- Individuals with asymptomatic sporadic NF-PNEN ≤ 2 cm
- Diagnosis has to be proven by a positive fine-needle aspiration (FNA) or by the presence of a measurable nodule on high-quality imaging technique (CT or MR) that is positive at ^68^Gallium DOTATOC-PET scan or Octreoscan.
- Patients who undergo surgery for NF-PNEN<2cm within 12 months. In these cases, diagnosis has to be proven by histological confirmation of NF-PNEN
- Informed consent

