## 6.1 Diagnostic work-up before inclusion

The goal of the diagnostic work-up is to characterize the neoplasm and to rule out other lesions (i.e. ductal adenocarcinoma, accessory spleen, solid serous cystadenoma). This work-up should have taken place no more than 12 months prior to inclusion. A high quality cross-sectional imaging study, either Computed Tomography (CT) or Magnetic Resonance Imaging (MRI) is mandatory. Diagnosis has to be proven by a positive fine-needle aspiration (FNA) or by the presence of a measurable nodule on high-quality imaging technique (CT or MR) that is positive at 68Gallium DOTATOC-PET scan or Octreoscan. Patients who undergo surgery for NF-PNEN<2cm within 12 months can also be enrolled. In these cases, diagnosis has to be proven by histological confirmation of NF-PNEN. CgA should be determined at treating physician’s discretion.

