**6.3 Data collection**

Treating physicians will be asked to fill case record forms (CRF). The following CRF will be provided:

- CRF 1: Diagnostic work-up before inclusion
- CRF 2: Active surveillance outcomes
- CRF 3: Surgical outcomes
- CRF 4: Pathological findings
- CRF 5: Follow-up after surgery

Patients will be asked to fill a questionnaire regarding the burden of NF-PNEN (Hospital Anxiety and Depression Scale – HADS) and two questionnaires regarding quality of life of patients with NF-PNEN (EORTC QLQ-C30 - version 3.0 and EORTC QLQ-GI.NET21). All three module will be administered at initial diagnosis, during surveillance and during follow-up after surgery at each visit.[^21^](#_ENREF_21) [^22^](#_ENREF_22) **(Appendix 4, Appendix 5, Appendix 6).**

Data will be recorded by the treating physician on a specific web-based site. Patients demographics will be not included in the CRF, and every patient will have an unique code, assigned by the treating centre, that will identify the Centre and the patient itself (e.g. SR001 San Raffaele Hospital patient number 1).

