### To evaluate the frequency of asymptomatic sporadic NF-PNEN ≤ 2 cm among overall sporadic NF-PNEN. Participating centers are required to give yearly the number of patients with NF-PNEN referred to their institution.

### The outcome of patients with an indication for NF-PNEN resection, in terms of the number of operated patients, surgical procedures, morbidity, mortality, and NF-PNEN recurrence.

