# STATISTICAL ANALYSIS

The first analyses will regard the data collected within the first 2 years. This report will contain purely descriptive statistics, according to the study endpoints described. The second analysis, after 5 years, will give an update of the first report and provide a more in depth analysis of the primary and secondary study endpoints.

Baseline patient and NF-PNEN characteristics will be described. Also, descriptive of the primary and secondary endpoints will be given. Depending on distributional properties of the observed variable, percentages, means ± standard deviation (SD), or medians with interquartile ranges (IQR) will be reported. Statistical significance will be assessed with use of the Student’s t-test for normally distributed continuous data; either the chi-square test for categorical data (with Yates’ correction when appropriate) or Fisher exact test for categorical data; and the median test for non-normally distributed continuous data. All reported p-values will be two-sided and a value < 0.05 will be considered to be significant. Data will be analysed with SPSS (SPSS Inc, Chicago, Illinois). For the primary endpoints, univariate comparisons will be conducted, to identify individual patient and NF-PNEN risk factors for progression/recurrence. As primary potential risk factors are considered; 1. NF-PNEN size at initial diagnosis, 2. NF-PNEN growth during follow-up, 3. serum CgA, 4.. Patient age, 5. Ki67.

Outcomes will be evaluated in the intention-to-treat population on the basis of treating physician-assessed tumor progression/recurrence. Survival analysis techniques and Cox regression with time-dependent recurrent covariates measures will be applied. Progression/recurrence is defined according to Response Evaluation Criteria in Solid Tumors (RECIST)[^23^](#_ENREF_23) version 1.0 criteria. In the surveillance group progression is defined as the appearance of distant metastases and/or local signs of invasiveness (I.e. vascular or nearby organs invasion). The mere tumor size increasing will be not considered a sign of progression unless it reaches > 2 cm of maximum diameter. The two groups of patients (active surveillance and surgical resection group) will not be directly compared. Rate of expect events is 0-10% for the two groups^19^ .

Multivariate survival analysis will only be performed if the number of events will be > 30. The potential risk factors, given above, will have first interest.

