**MANDATORY**

CT scan or MRI

^68^Gallium PET/CT Or Octreoscan

EUS+FNA

CgA + HADS + EORTC QLQ-C30 v3 and GI.NET21

Or histological confirm of NF-PNEN ≤ 2 cm

UPFRONT SURGERY OR ENROLLMENT*

* Date of surgery does not chance the timing of follow up that starts from the date of enrolment.

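### If patients may enter after resection, as the eligibility text most naturally allows, deaths between surgery and consent are lost, and operative mortality described over all operated patients is biased downward

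*Protocol*

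**What the plan says.** The surgical route into the study is set out in Protocol section 5.2: "Patients who undergo surgery for NF-PNEN<2cm within 12 months. In these cases, diagnosis has to be proven by histological confirmation of NF-PNEN". The same list requires "Informed consent" of every participant. Section 6.1, on the work-up before inclusion, repeats the route: "Patients who undergo surgery for NF-PNEN<2cm within 12 months can also be enrolled". Neither section says from which side of inclusion the 12 months are counted.

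Appendix 3, the scheme after resection, gives an alternative among its baseline items: "Or histological confirm of NF-PNEN ≤ 2 cm". It appears with the label "UPFRONT SURGERY OR ENROLLMENT". Section 6.3 says of the questionnaires: "All three module will be administered at initial diagnosis".

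The affected endpoint is in section 7, among the secondary endpoints: "The outcome of patients with an indication for NF-PNEN resection, in terms of the number of operated patients, surgical procedures, morbidity, mortality", followed by recurrence. No time window or denominator is attached to mortality. On analysis, section 8 says: "Also, descriptive of the primary and secondary endpoints will be given". It does not separate patients enrolled before their operation from those enrolled after it.

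**The concern.** If a patient can be enrolled on the histology of a resection already done, that patient must survive the operation and live long enough to consent. Operative deaths before consent drop out of both numerator and denominator, while survivors of the same operations stay in. Mortality described over all operated patients then depends partly on how late centres take consent, and not only on how safe the operation is.

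This matters because the stated aim is to find the most appropriate management of these small tumours, and operative death is a principal harm of choosing resection. The loss also cannot be repaired by analysing the enrolled cohort, because the missing patients are not in it.

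**Working it through.** **Which reading of the window?** Four points favour entry after surgery:
- The surgical route is separate from the aspiration and imaging routes, so the histology it asks for is most naturally the resection specimen.
- In section 6.1 it stands under a heading about work-up before inclusion, shortly after a rule that looks back 12 months from inclusion.
- Such patients are described as also eligible for enrolment.
- Appendix 3 accepts histology confirming size as well as type as a baseline alternative.

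Three points weigh against it or weaken it:
- Questionnaires are due at initial diagnosis.
- The study is called prospective.
- Appendix 2 also lists histological confirmation at the surveillance enrolment box, so histology at baseline does not by itself prove a prior resection.

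Entry after surgery is the more natural reading, but not a certain one.

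**Inputs.** The protocol gives no operative mortality, so there is no figure of its own to reproduce. The expected event rate of 0–10% in section 8 concerns progression or recurrence. All inputs below are assumptions:
- p: true operative mortality
- f: share of operated patients who could enter only after surgery
- g: share of operative deaths in that group that fall before consent
- N: number operated
- m: true morbidity, counting deaths as morbidity

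**Formula.** Per operated patient, deaths lost are pfg, deaths observed are p(1 − fg), and patients enrolled are 1 − pfg. Hence

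reported mortality = p(1 − fg) / (1 − pfg),

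which for small p is about p(1 − fg), a relative shortfall of about fg.

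**Example.** N = 300, p = 2%, f = 50%, g = 0.5. Expected deaths are 300 × 0.02 = 6. Expected lost are 6 × 0.5 × 0.5 = 1.5. Reported mortality is 4.5 / 298.5 = 1.51%.

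**Range at p = 2%:**

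| f | g = 0 | g = 0.5 | g = 1 |
|---|---|---|---|
| 20% | 2.00% | 1.80% | 1.61% |
| 50% | 2.00% | 1.51% | 1.01% |
| 80% | 2.00% | 1.21% | 0.41% |

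At f = 50%, p = 1% becomes 0.75% (g = 0.5) or 0.50% (g = 1), and p = 3% becomes 2.27% or 1.52%.

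**Morbidity.** Reported morbidity is (m − pfg) / (1 − pfg). With m = 30%, p = 2%, f = 50%, this is 0.295 / 0.995 = 29.65% at g = 0.5 and 0.290 / 0.990 = 29.29% at g = 1. It hardly moves.

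**Does the pooled interval still cover the truth?** The chance that the pooled exact 95% interval lies wholly below 2% was computed by summing over binomial lost and observed deaths, for f = 20%, 50%, 80%:

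| N | g = 0 | g = 0.5 | g = 1 |
|---|---|---|---|
| 150 | 0 | 0, 0, 0 | 0, 0, 0 |
| 300 | 1.7% | 2.8%, 6.0%, 12.4% | 4.6%, 19.6%, 66% |
| 500 | 1.0% | 2.0%, 5.8%, 14.9% | 4.1%, 26%, 86% |

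In most settings the interval still covers 2%, so the damage is mainly to the point estimate.

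**Is the enrolled-before-surgery group a better estimate?** It is free of this bias but smaller. Its standard error is √[p(1 − p) / (N(1 − f))]. At N = 300, p = 2%, f = 50% this is √(0.0196 / 150) = 1.14 percentage points. Root mean squared error at N = 300, in percentage points:

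| f, g | Pooled | Enrolled before surgery only |
|---|---|---|
| 50%, 0.5 | 0.86 | 1.14 |
| 80%, 0.5 | 1.01 | 1.81 |
| 20%, 1 | 0.83 | 0.90 |
| 50%, 1 | 1.15 | 1.14 |
| 80%, 1 | 1.64 | 1.81 |

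The restricted group is clearly ahead only at N = 500 with g = 1 and f of at least 50%: 0.89 against 1.09 at f = 50%, and 1.40 against 1.62 at f = 80%.

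**The case against.** The strongest reply is that two inferences are stacked: that consent can follow surgery, and that all operated patients are described together. The protocol states neither outright. Section 7 says mortality without calling it perioperative. How a descriptive endpoint is tabulated is commonly left to a statistical analysis plan, and nothing here forbids a split by entry route. The Appendix 3 flowchart has lost its layout in the available text, so which items belong to which box is partly reconstructed. The consent form, which was not available for this review, may fix when consent is taken. Every number above is assumed.

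Much of this stands, and it is why the point is conditional and minor. What it does not remove is the entry rule itself. The direction of an eligibility window belongs in the protocol, and no later tabulation restores patients who were never enrolled. Mortality is listed beside procedures and morbidity, which supports an operative meaning, and describing all operated patients together is the plain way to carry out the text.

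A reader might go further and infer that the protocol definitely enrols after surgery, or that every operative death on that route is lost. The documents do not support either. The window has no stated direction, and a patient who consents after surgery and then dies of a complication is counted.

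**Conclusion.** The concern holds in conditional form. If patients may consent after resection, and some operative deaths in that group precede consent, expected mortality over all operated patients is below the true value by a relative amount of about f × g. The direction follows from the consent requirement. The size cannot be fixed from the protocol: against an assumed 2%, the range shown runs from 2.00% (no deaths before consent) to 0.41% (f = 80%, g = 1). If all consent precedes surgery, f = 0 and there is no bias.

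Two further inferences are not supported. One is that this distorts a comparison of surgery with surveillance: section 8 says the two groups will not be directly compared, and no test uses this figure. The other is that patients enrolled before surgery should supply the only estimate: their figure is less precise, may reflect a different case mix, and often has the larger mean squared error.

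Severity is minor and confidence medium.

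**What to change.** In sections 5.2 and 6.1, state whether the 12 months run before or after inclusion, and hence whether consent may follow surgery.

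If entry after surgery is allowed, add to sections 7 and 8 that operative mortality and morbidity are reported by entry route, enrolled before versus after the date of surgery, with exact confidence intervals and alongside any pooled figure. Label both the post-surgery entrants and the pooled figure as conditional on survival to consent. Within the group enrolled before surgery, showing upfront surgery apart from surgery after surveillance would help readers judge case mix.

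The cost is wording and one split by enrolment date against surgery date, both of which section 6.2 already refers to. No new visits are needed. The downside is smaller denominators and wider intervals in each group. With 300 operated and 2% mortality, f = 50% leaves 150 enrolled before surgery, and 3/150 = 2.0% has an exact 95% interval of 0.4% to 5.7%. With f = 80% only 60 remain, and 1/60 = 1.7% has an interval of 0.04% to 8.9%.

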### NF-PNEN evolution, in terms of development of symptoms, tumour growth, development of distant metastases and secondary pancreatic duct dilatation.

### The perceived burden of surveillance or follow-up after surgery for participants, as assessed by questionnaires regarding attitude towards surveillance and general anxiety and depression (Hospital Anxiety and Depression scale, HADS[^22^](#_ENREF_22)). Moreover we ask patients to fill out EORTC QLQ-C30 (version 3) and EORTC QLQ-GI.NET21 Module.

# STATISTICAL ANALYSIS

The first analyses will regard the data collected within the first 2 years. This report will contain purely descriptive statistics, according to the study endpoints described. The second analysis, after 5 years, will give an update of the first report and provide a more in depth analysis of the primary and secondary study endpoints.

Baseline patient and NF-PNEN characteristics will be described. Also, descriptive of the primary and secondary endpoints will be given. Depending on distributional properties of the observed variable, percentages, means ± standard deviation (SD), or medians with interquartile ranges (IQR) will be reported. Statistical significance will be assessed with use of the Student’s t-test for normally distributed continuous data; either the chi-square test for categorical data (with Yates’ correction when appropriate) or Fisher exact test for categorical data; and the median test for non-normally distributed continuous data. All reported p-values will be two-sided and a value < 0.05 will be considered to be significant. Data will be analysed with SPSS (SPSS Inc, Chicago, Illinois). For the primary endpoints, univariate comparisons will be conducted, to identify individual patient and NF-PNEN risk factors for progression/recurrence. As primary potential risk factors are considered; 1. NF-PNEN size at initial diagnosis, 2. NF-PNEN growth during follow-up, 3. serum CgA, 4.. Patient age, 5. Ki67.

Outcomes will be evaluated in the intention-to-treat population on the basis of treating physician-assessed tumor progression/recurrence. Survival analysis techniques and Cox regression with time-dependent recurrent covariates measures will be applied. Progression/recurrence is defined according to Response Evaluation Criteria in Solid Tumors (RECIST)[^23^](#_ENREF_23) version 1.0 criteria. In the surveillance group progression is defined as the appearance of distant metastases and/or local signs of invasiveness (I.e. vascular or nearby organs invasion). The mere tumor size increasing will be not considered a sign of progression unless it reaches > 2 cm of maximum diameter. The two groups of patients (active surveillance and surgical resection group) will not be directly compared. Rate of expect events is 0-10% for the two groups^19^ .

Multivariate survival analysis will only be performed if the number of events will be > 30. The potential risk factors, given above, will have first interest.

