# STUDY DESIGN

The study is designed as a prospective international (including also non-European institutions) multicentre cohort study, which will be coordinated by the Pancreatic Surgery Unit of San Raffaele Scientific Institute (Lead Study Centre) under the auspices of the European Neuroendocrine Tumor Society (ENETS).

The study duration is 6 years, patients will be recruited for 5 years from December 2016 to December 2021, with a follow up of 1 year at least (end of the study: December 2022). After 2 years of recruitment an interim analysis will be performed in December 2018. San Raffaele Scientific Institute will be the lead centre from where the international study will be managed and coordinated. Participating study centre will identify, recruit patients and will send pseudoanonimised data of patients to the lead centre, which is responsible for statistical analysis, storing and controlling data. The research database will be managed and analysed by the Lead Study centre research team. Study participation is voluntary, there will be no reimbursement for patients.

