# METHODS

## Study Endpoints

### Main study endpoint

### The primary endpoint is disease/progression-free survival, defined as the time from study enrolment to the first evidence of progression (surveillance group) or recurrence of disease (surgery group) or death from disease.

### Secondary study endpoints

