**OPTIONAL or MANDATORY if Ki67>2%**

CT scan or MRI

CgA + HADS+ EORTC QLQ-C30 v3 and GI.NET21

6 Months

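### Endpoints that accrue over time are to be summarised as percentages, means or medians despite unequal follow-up, and survival methods are not stated to cover the first report or the tumour-evolution endpoints

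*Protocol*

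**What the plan says.** Section 8 of the protocol plans two analyses. Of the first, on the data of the first two years, it says "This report will contain purely descriptive statistics, according to the study endpoints described". Of the later one: "The second analysis, after 5 years, will give an update of the first report", together with a deeper analysis of the endpoints.

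For the summaries it says "Also, descriptive of the primary and secondary endpoints will be given", and then fixes their form: "Depending on distributional properties of the observed variable, percentages, means ± standard deviation (SD), or medians with interquartile ranges (IQR) will be reported".

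The same section later names survival methods and a Cox model with time-dependent covariates. That sentence stands beside the definition of progression and recurrence. It does not say which report or which secondary endpoints it covers.

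Section 7 makes the primary endpoint a time to event, "defined as the time from study enrolment to the first evidence of progression (surveillance group) or recurrence of disease (surgery group) or death from disease". The secondary endpoints include recurrence after resection and tumour evolution: new symptoms, growth, distant metastases and duct dilatation.

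On timing, section 4 gives recruitment from December 2016 to December 2021, study end in December 2022, and "After 2 years of recruitment an interim analysis will be performed in December 2018".

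On imaging under surveillance, section 6.2 advises 6-monthly studies for two years and makes CT or MRI mandatory at least yearly. Appendix 2 marks the 6- and 18-month visits "OPTIONAL or MANDATORY if Ki67>2" per cent.

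**The concern.** The form of the summary is to be chosen by the distribution of the variable. That criterion takes no account of how long each patient has been observed. For an endpoint that builds up over time, a percentage of enrolled patients depends on when they joined as well as on the disease.

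Unequal follow-up is built into the design. At the first report recruitment is still open, so some patients have just enrolled and others have two years. Under even accrual half have less than 12 months, and Appendix 2 does not yet require a follow-up scan of them unless Ki67 is above 2%. In a plain percentage they count as event-free.

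The background section says that the evidence on surveillance is retrospective and that management is still debated. Risk figures under surveillance are therefore among the most important things this cohort can supply, and a figure with no horizon cannot be compared with other series or used to counsel a patient.

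**Working it through.** The protocol gives no figure of its own on this point, so there is nothing to reproduce. The check asks what a crude percentage would show.

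**Inputs from the protocol**
- First report: December 2016 to December 2018, so follow-up is 0 to 24 months.
- Study end: December 2022 with recruitment to December 2021, so follow-up is 12 to 72 months.
- Scans under surveillance: yearly (mandatory minimum) or 6-monthly in the first two years (advised).

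**Assumptions**
- Even accrual.
- Constant hazard of 2% per year. Section 8 expects 0-10% events without a horizon; 2% per year gives 9.5% at five years, near the top of that range. The protocol gives no rate for growth, symptoms or duct dilatation, so for those endpoints the figures are only illustrative.
- An event is detected at the next scheduled scan, and the denominator is all enrolled patients.

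**True risk**, F(t) = 1 − exp(−0.02t), t in years:
- 6 months 1.00%, 12 months 1.98%, 18 months 2.96%, 24 months 3.92%
- 36 months 5.82%, 48 months 7.69%, 60 months 9.52%

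**First report**
- Yearly scans only: half the patients have had no follow-up scan and half have had only the 12-month scan. Crude = ½ × 0 + ½ × 1.98% = 0.99%.
- 6-monthly scans: a quarter each have a last assessment at 0, 6, 12 and 18 months. Crude = (0 + 1.00 + 1.98 + 2.96)/4 = 1.48%.
- Continuous detection: crude = 1 − (1 − e^−0.04)/0.04 = 1.97%.

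Against the 12-month risk of 1.98%, the crude figure is too low by a factor of 2.0 with yearly scans and 1.3 with 6-monthly scans. With continuous detection it is not too low, because mean follow-up is then 12 months. The factor of 2.0 does not depend on the hazard: the crude figure is half of F(12 months) whatever its value.

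**Study end, 12 to 72 months, yearly scans**
- A fifth each have a last scan at 12, 24, 36, 48 and 60 months. Crude = (1.98 + 3.92 + 5.82 + 7.69 + 9.52)/5 = 5.79%.
- This is about the 36-month risk (5.82%). It lies above the 12- and 24-month risks and below the 60-month risk (9.52/5.79 = 1.6).

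**Date of the second analysis**
Section 8 places it after 5 years, which could mean December 2021 rather than study end. Follow-up would then be 0 to 60 months and, with yearly scans, crude = (0 + 1.98 + 3.92 + 5.82 + 7.69)/5 = 3.88%. That is close to the 24-month risk. The same wording in the plan thus yields a percentage tied to a different horizon at each data cut.

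**The case against.** The strongest reply is that section 8 does name survival methods, does not confine them to the second analysis, and defines the primary endpoint as a time. A Kaplan-Meier curve is itself descriptive, so the first report could contain one. The sentence on percentages, means and medians is general, covers baseline data too, and sets no denominator. Horizons and censoring rules are commonly left to a statistical analysis plan, which may exist.

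Part of this stands. The survival sentence reasonably reaches progression and recurrence at the final analysis, and a percentage labelled as observed to date, with follow-up stated, would not be wrong. But the protocol is not silent. It states a form of summary for these endpoints, requires no such label, and does not extend the survival methods to the first report or to tumour evolution.

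Three stronger readings are tempting, and the documents do not support them.
- **A reader might infer a four-fold understatement in the first report**, from 0.99% against the 24-month risk of 3.92%. This needs even accrual, yearly scans only and a 24-month comparator together. In that scenario nobody has been assessed beyond 12 months, so no method could estimate the 24-month risk. Nor is four a ceiling: accrual that rises over time would give a larger ratio.
- **A reader might infer that crude figures always make the risk look smaller.** The direction depends on the horizon: the 5.79% at study end exceeds the 12- and 24-month risks.
- **A reader might infer that the primary endpoint is left to crude percentages throughout.** At the final analysis the survival methods reasonably cover it.

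**Conclusion.** The point holds in a limited form. For the first report, and for the evolution endpoints in both reports, following the text gives percentages with no time horizon, drawn from patients with very different follow-up. Under the stated assumptions the first-report figure is 1.0% to 1.5% against a 12-month risk of 2.0%, with no gap if detection were continuous. At study end the crude figure of 5.8% reads as roughly a 36-month risk, against 9.5% at 60 months; this bears on the evolution endpoints and accompanying descriptive tables, not on the survival analysis of the primary endpoint. The sizes rest on assumed even accrual, a constant hazard and the scan schedule. It is a cheap improvement that does not put the study's main analysis in doubt.

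**What to change.** Add to section 8 that, for the primary endpoint, recurrence after resection and the evolution endpoints, both reports give Kaplan-Meier or cumulative incidence estimates at fixed times, with numbers at risk, 95% confidence intervals and median follow-up. Specify:
- Horizons that the follow-up supports: 12 months in the first report, and 24 months only if enough patients have been assessed that far; 12, 24, 36 and 60 months at the end.
- Censoring at the last assessment.
- How death and resection are handled for each endpoint.
- The date of the second data cut, since 60 months is supported by a December 2022 cut but hardly by one in December 2021.

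Percentages, means and medians can stay for baseline data and for items that do not accrue over time, such as type of operation.

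The cost is a few sentences, with the same data and standard output, and the first report stays descriptive. Its estimates become less precise. If 1000 patients accrue evenly, 1000 × 2/5 = 400 are enrolled by December 2018 and about 200 have reached 12 months. With yearly scans throughout, the standard error of a 12-month risk of 1.98% is √(0.0198 × 0.9802/200) = 1.0 percentage point, against √(0.0099 × 0.9901/400) = 0.5 for the crude figure. Reported risks may also look less favourable.

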**5.4 Sample Size Calculation**

Based on a reported incidence rate of PNEN of 0.4/100.000 inhabitants[^5^](#_ENREF_5) [^20^](#_ENREF_20) and considering a rate of PNEN<2cm of 20%, we estimate an incidence of around 580 PNEN<2cm per year only in Europe. Worldwide the estimation of new PNEN<2 cm is around 29840 cases in five years. In the study period we aim to include at least 1000 patients during the study period.

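### The median test named for skewed continuous data is valid but costs about a third of the information for typical right-skewed variables; the rank-sum test is a cheap improvement

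*Protocol*

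**What the plan says.** The Statistical Analysis section lists its significance tests by type of variable: Student's t-test for normal continuous data, chi-square or Fisher's exact test for categorical data, and "the median test for non-normally distributed continuous data". The level is 5%: "All reported p-values will be two-sided and a value < 0.05 will be considered to be significant". Where the distribution calls for it, "medians with interquartile ranges (IQR) will be reported".

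For the primary endpoint, "univariate comparisons will be conducted, to identify individual patient and NF-PNEN risk factors for progression/recurrence". The factors listed are tumour size at diagnosis, growth during follow-up, serum CgA, age and Ki67. The section then adds: "Survival analysis techniques and Cox regression with time-dependent recurrent covariates measures will be applied". It also states: "The two groups of patients (active surveillance and surgical resection group) will not be directly compared". Multivariable survival analysis is conditional on more than 30 events.

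Two figures set the likely size of any comparison by event status. Section 5.4 says "we aim to include at least 1000 patients during the study period", and the Statistical Analysis section says "Rate of expect events is 0-10% for the two groups".

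**The concern.** The median test reduces each value to one bit, above or below the pooled median, and compares the two proportions. The rank-sum test uses the full ordering. For a right-skewed variable whose distribution shifts on the log scale, the ordering carries information that the median test discards. CgA and Ki67, both listed as risk factors, are plausibly of this kind.

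The loss would matter most where one group is small. With 0 to 10% events, a comparison of patients with and without an event has at most about 100 of 1000 patients in the smaller group. If 30 or fewer events occur, no multivariable model is fitted and the univariate results are the only risk-factor evidence. The section does not say whether those univariate comparisons are Cox models or the two-sample tests listed just before them. If they are two-sample tests, real differences in skewed factors would more often be reported as not significant. The same applies to any significance test on skewed baseline, secondary or questionnaire data.

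**Working it through.** The protocol gives no power, effect size or standard deviation for any two-sample test, so there is no figure of its own to reproduce.

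**Inputs from the protocol.** Two-sided alpha 0.05 (Statistical Analysis); 1000 patients (section 5.4); 0 to 10% events, so 0 to 100 events (Statistical Analysis).

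**Assumptions.** Lognormal data, a shift *d* of 0.4 SD on the log scale, 30, 50 or 100 events, complete data on the variable, and no continuity correction.

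**Step 1: asymptotic relative efficiency (ARE).** For a shift in a density *f* with median *m*, the ARE of the median test against the rank-sum test is

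4 f(m)² / [12 (∫f²)²].

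Both tests are unchanged by taking logs, so the lognormal case is the normal case on the log scale. There f(m)² = 1/(2π) = 0.1592 and ∫f² = 1/(2√π) = 0.2821, so

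ARE = (4 × 0.1592) / (12 × 0.0796) = 0.637 / 0.955 = 0.667.

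**Step 2: what this means at 80% power.** A rank-sum test with 80% power has standardised effect 1.960 + 0.842 = 2.802. The median test has 2.802 × √0.667 = 2.288. Its power is Φ(2.288 − 1.960) = Φ(0.328) = 62.8%, a loss of about 17 points.

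**Step 3: power at the protocol's numbers.** For the rank-sum test, power = Φ(d × √12 × ∫f² × √(n₁n₂/N) − 1.960). For the median test, power is that of comparing p₁ and p₂, the shares above the pooled median, with SE₀ the standard error under no difference and SE₁ the standard error under the shift: Φ((p₁ − p₂ − 1.960 SE₀)/SE₁).

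For 50 against 950:
- Rank-sum: 0.4 × 0.977 × 6.892 = 2.694; Φ(2.694 − 1.960) = 76.9%.
- Median test: p₁ = 0.648, p₂ = 0.492, SE₀ = 0.0725, SE₁ = 0.0695; Φ((0.156 − 0.142)/0.0695) = 57.9%.

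| Events / no event | Rank-sum | Median test | Loss by formula | Loss by simulation |
|---|---|---|---|---|
| 30 / 970 | 55.9% | 38.5% | 17 | 20 (55% vs 35%) |
| 50 / 950 | 76.9% | 57.9% | 19 | 15 (75% vs 60%) |
| 100 / 900 | 96.0% | 85.3% | 11 | 11 (96% vs 85%) |

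The loss is therefore about 11 to 20 points at 0.4 SD. Over shifts of 0.3 to 0.5 SD and the same event counts, the formulas give 3 to 20 points. The smallest loss is at 100 events and 0.5 SD, where both tests are near full power (99.6% against 96.5%).

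**Step 4: sensitivity to shape.** With the rank-sum test at 80% power, the ARE and the resulting median-test power are:

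| Shape | ARE | Median-test power |
|---|---|---|
| Exponential, scale change | 0.641 | 61.1% |
| Lognormal, log-scale shift | 0.667 | 62.8% |
| Logistic | 0.75 | 67.9% |
| t with 3 df | 0.853 | 73.5% |
| Laplace | 1.333 | 89.9% |
| Exponential, location shift | 0.333 | 36.6% |

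The direction holds for the usual right-skewed shapes and reverses for the Laplace shape.

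**Step 5: what the median test offers in return.** With equal medians but different spread or shape (50/950 and 100/900, 3000 simulated samples each), the rank-sum test rejected in 13% to 46% of samples and the uncorrected median test in 4% to 7%.

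**The case against.** The strongest reply is that nothing here is an error. The median test is valid, it targets the same quantity that the section reports for skewed data, and no stated power or sample size depends on it. Preferring a more efficient valid test is partly a matter of taste. The harm is also limited: the outcomes have survival methods and Cox regression, and the two management groups are not compared. If the univariate risk-factor comparisons are Cox models, the loss calculated above does not arise there. CgA and Ki67 may also be incomplete, because diagnosis can rest on imaging alone and section 6.1 leaves CgA to the physician's discretion (although Appendix 2 lists it at enrolment). The group sizes used above are then optimistic for those two variables.

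Most of this stands, and it keeps the severity low. It does not remove the point, because the protocol itself fixes the less efficient test and gives no reason.

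A reader might go further in three ways that the documents do not support:
- *That most of the information is lost.* For lognormal or gamma-type data it is about a third. Only extreme cases, such as an exponential location shift, lose more than half.
- *That the plan carries a definite power loss.* It states no effect size or distribution, and plausible settings run from a gain of 5 to 10 points to a loss of about 40. Yates' correction would enlarge some losses, but the protocol attaches it to the chi-square test for categorical data; using it inside the median test is an assumption.
- *That the rank-sum test has the same assumptions and the median test no advantage.* Step 5 shows otherwise, and the median test can win with heavy tails.

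**Conclusion.** The point holds as a cheap improvement of low severity. For the right-skewed variables this study is likely to meet, the named test gives up about a third of the information (ARE about 2/3 if lognormal). Under the assumed 0.4 SD log-scale shift with 30 to 100 events in 1000, that is about 11 to 20 points of power. The figures depend on the assumed shape, effect and complete data. The choice bears on baseline, secondary and questionnaire comparisons, and on the univariate risk-factor comparisons only if these are two-sample tests. No primary conclusion is shown to change.

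**What to change.** In the Statistical Analysis section, replace the median test with the Wilcoxon rank-sum (Mann-Whitney) test for non-normally distributed continuous data. State in the same paragraph that risk factors for the time-to-event primary endpoint, including the univariate ones, are tested with Cox models.

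Add one sentence on interpretation: the rank-sum test compares whole distributions, so where spread or shape differs between groups a significant result is not strictly a difference in medians. If the investigators want a test of medians for that reason, they can keep the median test and say why.

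The cost is one phrase and one or two sentences, with no new data and no change of software.
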